### Group 1: DVD/web format

The intervention comprises five modules:Module 1 - *Complementary medicine - the evidence.* This module provides scientific evidence related to the health benefits of CM, its indications, and details of various evidence-based CM that are widely practiced globally.Module 2 - *Finding and evaluating complementary medicine evidence*. This module provides an introduction to scientific evidence and how to find research-based studies about CM. It describes databases that are available to find research, how to conduct a search, and how to use the available evidence in making an informed choice about CM.Module 3 - *Decision making – complementary medicine.* In this module, advice is provided regarding how to bring together the information they have obtained from earlier modules, aligning this with their goals and values, and how to have discussions with relevant key people to make an informed decision about the use of CM. The universally employed situation, choices, objectives, people, evaluation, and decisions (SCOPED) framework [29] has been incorporated to assist the participant in their decision making.Module 4 - *Working with complementary medicine practitioners*. This module explains the role of conventional healthcare providers and CM practitioners, and the importance of, and how to disclose CM use with conventional health providers. Guidance is provided regarding the regulatory frame work for CM practitioners in Australia, how to find a professionally accredited CM practitioner and practical tips and questions to ask to guide the selection of a CM practitioner.Module 5 - *Monitoring complementary medicine decisions*. This module explains the need to monitor one’s health following the use of CM products or therapies. It provides guidance on certain criteria that should be utilised in respect to monitor one’s health and the safety of CM and the procedure (including contact details) of adverse events reporting for CM therapy and services in Australia. There is a final section that includes two case studies of individuals exploring self-care and use of CM that draws on the detailed information presented in the modules.

Participants in the intervention group will be invited to watch the five-module intervention in their home by either accessing a website using a password, or viewing a DVD player or computer, over a 3-week time period. Each module takes approximately 30 minutes to complete, and completion of two modules per week over 3 weeks is recommended. Users will be able to pace their learning using the navigation menus on the website or DVD. Participants are able to access the intervention as often as they wish. They will also receive a copy of the booklets.

### Group 2: control group

The active control group comprises two booklets including summarised content from modules one, three, five and the case studies. The content focuses on presenting information on evidence-based CM modalities, guidance to sourcing reliable CM information, how to make decisions about evidence-based CM, why it is important to monitor and evaluate the use of CM, and details about how to discuss CM use with your healthcare provider. A second booklet provides written examples of the two case studies, and applying the information into practice. The booklet text is written in 18-point Arial font and at a 6th-grade reading level. Paced reading is encouraged over the 3-week intervention.

### Development and piloting of the intervention

The investigators undertook development, proofing and editing of the web materials and booklet, with the assistance of web and communication officers at Western Sydney University. Following development of the modules and booklet, a pilot study was undertaken for preliminary testing of the educational and assessment tools. Four participants were presented with the booklet or access to the website to review the booklet or selected web-based modules. Participants were requested to read the allocated resources and to complete a short feedback form on the content of the resources, ease of understanding the material, did they feel overwhelmed by the amount of content, did the images help them to engage with the material, was the font size and layout appropriate, and was the website easy to navigate? The participants were also invited to come together in a focus group context to discuss the resources. The group session was led by GG and the interview guide included questions about ease of use of the educational materials (i.e. font size, colour, background, instructions), and how long it took participants to complete the modules. For those using the website specific questions were asked about where they accessed the website, and what did they use (i.e., tablet, laptop, desktop). Participants were also asked about the ease of understanding the concepts presented.

Feedback from the focus groups indicated participants found the information useful and interesting, they enjoyed the interactive, engaging and colourful format of the resources, the modules did not require as much time as expected to complete, and they enjoyed accessing the resources in their own time. The baseline questionnaire was also pilot tested with the focus group and as a result small wording and skip logic changes were undertaken to the instruments.

### Procedure for the trial

Following completion of the pilot and minor modification to the resources, recruitment for the main trial commenced in July 2016. Recruitment will be undertaken at all interested retirement villages. Study promotion will involve letter box drops, and promotional talks by the investigators and the trial co-ordinator. At these visits, following a promotional study presentation, expressions of interests will be gathered and participant information and consent forms made available. A mutually convenient time will be made to obtain informed consent and to complete baseline questionnaires.

Following randomisation, the trial co-ordinator will meet with each participant to ensure they are able to access the website using the password and to navigate the modules, or ensure navigation with the DVD is satisfactory. To minimise attrition, all groups will receive a phone call mid-way through the intervention to ensure they are continuing to access the resources and address any difficulties. Primary and secondary outcome data will be collected at baseline, at the end of the intervention and at two months from trial entry. At trial entry we will collect baseline data on socio-demographic (age, gender, place of birth, education status, employment status, ethnicity, English skills, Medicare and private health insurance) and health characteristics, health behaviour, and lifestyle including CM use, sources of information, Internet skills, health literacy status, and decision-making (Fig. 2: SPIRIT figure).

**Fig. 2 Fig2:**
[figure not shown]
Standard protocol items: recommendation for interventional trials (SPIRIT) schedule of enrolment, interventions, and assessments

### Data management

Data capture will be via paper-based questionnaires. Data will be manually entered onto the electronic REDCap data management system by the trial co-ordinator. Any issues will be discussed at the weekly research meeting. All entered data will be de-identified.

### Primary outcome measure

#### Decision self-efficacy

The primary outcome is the change on decision self-efficacy at the end of the intervention assessed between groups. The Decision Self-Efficacy scale [30] will be used to assess differences in decision-making skills. The Decision Self-Efficacy scale will measure self-confidence or belief in one’s ability to make decisions, including an ability to participate in shared decision making. This scale comprises 11 items rated along a 5-point scale from “not at all confident” to “very confident”. The psychometric properties report an alpha coefficient of 0.92, and the scale has been shown to be correlated with decisional conflict scales (DSC) of feeling informed (0.47) and supported (0.45) [32]. Scores on the scale are converted to a 0–100 scale. Scores range from 0 (extremely low self-efficacy) to 100 (extremely high self-efficacy).

### Secondary outcome measures

The preparation for the decision-making scale assesses a participant’s perception of how useful a decision aid or other decision support intervention is in preparing the individual to communicate with their practitioner at a consultation focused on making a health decision [31]. The scale addresses concepts of preparedness for decision making and consists of 10 items rated along a 5-point scale from “not at all” to “a great deal”. This scale has shown significant correlation with the informed (*r* = − 0.21, *p* < 0.01) and support (*r* = − 0.13, *p* = 0.01) DSC subscales [32], and discriminates significantly between participants who did and did not find the decision aid helpful (*p* < 0.0001). Alpha coefficients for internal consistency ranged from 0.92 to 0.96. The scale is strongly unidimensional and item response theory analyses demonstrated that all ten scale items perform well [31]. The scale is only administered after the intervention has been administered, and the items are summed, scored and converted to a 0–100 scale. Higher scores indicate a higher perceived level of preparation for decision making.

The health literacy of participants will be evaluated using a validated and universally employed Health Literacy Questionnaire (HLQ) [14]. The HLQ contains a total 55 questions grouped into nine domains including: (1) feeling understood and supported by healthcare providers; (2) having sufficient information to manage personal health; (3) an ability to actively manage personal health; (4) social support for health; (5) appraisal of health information; (6) ability to actively engage with health care providers; (7) navigating the health care system; (8) ability to find good health information; and (9) understanding health information well enough to know what to do. Each scale includes four to five items, with participants indicating their response along a Likert-type scale with response options ranging from 1 - “very difficult” to 4 - “very easy”, or along a 5-point scale ranging from “strongly agree” to “strongly disagree.” The HLQ has strong psychometric properties, it is grounded in the individual’s lived experience, and is validity driven [14]. Reliability testing was examined using Raykov’s procedures rather than Cronbach’s alpha where > 0.80 was sought. This was achieved for eight of the nine domains; the lowest reliability estimates were achieved for the appraisal of information (0.77). Health literacy scales will be calculated using a scoring algorithm for the HLQ version 1 (dated 2012). The algorithm produces unweighted scale scores for the nine scales of the HLQ, with the final score for each subscale an average score across all items forming the scale. For missing values, this programme uses an algorithm to impute missing values. For scales with four to five items, two missing values can be imputed. For scales with six items, three missing value can be imputed, and if more responses among the scale items were missing, scale score were not computed.

Health-seeking behaviour will be assessed by responses to questions on use of self-care and CM. It will be assessed through a self-reported questionnaire based on questions relating to use of health information sources. Perception of risk will ask questions about the safety of CM. To evaluate the intervention we are seeking participants’ views on the ease of using the resources, the length of the modules, the amount of information and participant understanding of the modules and written information. We will ask participants if they have used the resources outside of the intervention, and if yes, how easy or difficult this was, and did the resources assist with making an informed decision. All data forms will be completed by study participants.

### Statistical analysis

The trial co-ordinator will co-ordinate all data management and cleaning prior to analysis. Data on refusal and dropout will be coded and reported according to Consolidated Standards of Reporting Trials (CONSORT) guidelines [33, 34]. A description of the baseline characteristics of study participants will be compiled using descriptive statistics, such as mean, standard deviation for continuous variables and categorical variables will be summarised by counts and percentages.

The primary analysis will be conducted using all randomised participants. The chi square (*X*
^2^) test and analysis of variance (ANOVA) will be used to identify the differences between intervention groups for the categorical and continuous variables respectively. Secondary analyses will examine changes within group over time using repeated measures ANOVA and the Sidak test to correct for multiple comparisons [35]. Levels of significance will be reported at the *p* < 0.05 level. All CIs will contribute to data interpretation. All analyses were conducted using SPSS statistical software, version 22. The results from this unblended trial will be critically evaluated for bias, and this will be considered during interpretation of the results.

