### Sample size calculation

The sample size was calculated using GPower, and was based on “sample size effect” drawn from published data [23]. It was estimated that a moderate effect size would be obtained (i.e. Cohen *D* = 0.5) for the primary endpoint only, with improved decision self-efficacy between groups at the end of the 3-week intervention. With the alpha value set at 0.05 and power at 0.8 (i.e. 80% chance that the expected effect size would be significant), a minimum sample size of 64 per group, with rounding to 70 per group was estimated. Allowing for 20% attrition, a total sample size of 168 participants was required for this trial (i.e. 84 per group).

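### The primary analysis is labelled as using all randomised participants, but plain ANOVA omits anyone without a 3-week score and the plan allows for 20% attrition

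*Protocol article*

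**What the plan says.** The Statistical analysis section fixes the analysis set: "The primary analysis will be conducted using all randomised participants". The next sentence fixes the method, a chi-square test or ANOVA: "analysis of variance (ANOVA) will be used to identify the differences between intervention groups for the categorical and continuous variables respectively". Repeated measures ANOVA has a different role: "Secondary analyses will examine changes within group over time using repeated measures ANOVA".

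The Decision self-efficacy section defines the endpoint: "The primary outcome is the change on decision self-efficacy at the end of the intervention assessed between groups". Each analysed participant therefore needs both a baseline and a 3-week questionnaire.

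The Sample size calculation section expects losses: "Allowing for 20% attrition, a total sample size of 168 participants was required for this trial (i.e. 84 per group".

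On missing data, Secondary outcome measures gives a rule for missing items within HLQ scales. The Statistical analysis section says that refusals and dropouts will be coded and reported under CONSORT. The article gives no rule for a missing Decision Self-Efficacy score or a missing questionnaire.

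**The concern.** The article states both who is analysed and how, and as written the two do not fit. An ANOVA on observed scores cannot include a person who has none, and nothing in the article supplies a score for that person. A reader would take the primary result to cover everyone randomised, when the stated procedure covers completers only.

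The stake is bias. The arms ask for different effort: five modules of roughly half an hour each by web or DVD plus booklets, against booklets alone. Participants know their allocation. Dropout could therefore differ between arms in amount or in kind, although the article gives no figures on this. If low-confidence participants leave one arm more than the other, the completers are no longer comparable at baseline, and neither a change score nor a raw 3-week score corrects for that.

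Separately, and only for the secondary analyses, a standard repeated measures ANOVA across three visits drops anyone who misses any one of them.

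**Working it through.** **1. The plan's own figures.** Inputs from Sample size calculation: d = 0.5, alpha 0.05, power 0.80, 64 rounded to 70 per group, 20% attrition, 84 per group. A two-sided two-sample t-test (noncentral t) needs 63.77, so 64 per group, which reproduces the stated minimum. The 84 is reproduced as 70 × 1.2 = 84, and 2 × 84 = 168.

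**2. How many would be missing.**
- 20% of 168 is 33.6, about 34. This leaves 84 × 0.8 = 67.2, about 67 per group.
- Counting instead from the 70 per group that the plan wants to keep: 2 × (84 − 70) = 28.
- Both are upper figures for the primary endpoint, because the article does not say how much of the attrition falls before 3 weeks and how much between 3 weeks and 2 months.

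**3. Power.** For d = 0.5, two-sided alpha 0.05: 0.801 with 64 per group, 0.819 with 67, 0.836 with 70 and 0.896 with 84. The target of 0.80 is met with completers only.

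**4. Bias when dropout depends on baseline in one arm (illustration; all inputs assumed).** Baseline X and 3-week score Y are bivariate normal with unit SD and correlation r. In the intervention arm the log odds of dropout rise by ln(OR) per SD lower X, with the intercept set to give dropout rate p. In the control arm dropout is completely at random. Let m be the mean of X among intervention completers, in SD:

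m = ∫ z·(1 − π(z))·φ(z) dz / (1 − p), where π(z) is the dropout probability at X = z.

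Bias of the completer difference is r·m for the raw 3-week score and (r − 1)·m for the change score. Numerical integration gives:

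| OR | p | m | change score, r = 0.3 / 0.5 / 0.7 | raw score, r = 0.3 / 0.5 / 0.7 |
|---|---|---|---|---|
| 1.5 | 0.20 | 0.079 | -0.055 / -0.039 / -0.024 | +0.024 / +0.039 / +0.055 |
| 1.5 | 0.25 | 0.098 | -0.069 / -0.049 / -0.030 | +0.030 / +0.049 / +0.069 |
| 3 | 0.20 | 0.186 | -0.130 / -0.093 / -0.056 | +0.056 / +0.093 / +0.130 |
| 3 | 0.25 | 0.228 | -0.160 / -0.114 / -0.068 | +0.068 / +0.114 / +0.160 |

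The unit is the SD of a score at one visit. A simulation of 2,000,000 subjects with OR = 3 and p = 0.25 agrees with the last row, and adjusting for baseline brings the bias to 0.00 at each r.

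**5. When the arms behave more alike.** With OR = 3 in both arms but 25% against 15% dropout, m is 0.228 and 0.142, a difference of 0.086. The change-score bias is then -0.06, -0.04 and -0.03 SD. With the same rate and mechanism in both arms, the two values of m cancel and the bias is zero.

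**6. What baseline cannot repair.** If intervention non-completers are worse than completers by 0.25 to 0.5 SD for reasons that baseline does not capture, at 20% missing in that arm only, the bias is 0.25 × 0.2 = 0.05 to 0.5 × 0.2 = 0.10 SD in favour of the intervention.

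**The case against.** The strongest objection is that this is missing detail. ANOVA compares groups once every person has a score and can follow imputation; a condensed article may leave that step to a full protocol or analysis plan that is not shown. This stands in part: a reader might infer that no imputation was planned, and the article does not establish that. The point rests instead on what the article does state, a population and a method that do not match without an unstated step.

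The sentence may also have been meant as analysis by allocated group. That is a reasonable reading, but the text does not say it.

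Three stronger readings are tempting and are not supported:
- That repeated measures ANOVA turns the primary analysis into complete cases. It is assigned to secondary, within-group analyses, and a missing 2-month score cannot affect a 3-week between-group contrast.
- That the benefit would be inflated by up to about a third of the planned effect. The largest positive figure, +0.16 SD, is for raw 3-week scores. The defined outcome is change, for which the same scenario gives a negative bias, against the intervention.
- That power is lost. It is not, at the planned attrition.

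The article also plans a mid-intervention call to limit attrition and promises a critical evaluation of bias. Both are useful, but neither says how participants without a score enter the analysis.

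**Conclusion.** The point holds in this form: followed as written, the primary analysis uses participants with observed scores and does not match its all-randomised label. Up to about 34 of 168 participants are affected, if attrition is 20% and all of it falls by 3 weeks.

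The consequence is possible bias, and it is conditional. With dropout of 20% to 25% related to baseline in the intervention arm only, odds ratio 1.5 to 3 per SD and r from 0.3 to 0.7, the bias is about -0.02 to -0.16 SD for the change score. For the raw 3-week score it is the mirror image, +0.02 to +0.16 SD. For scale, the design effect is 0.5 SD, though the article does not say whether that SD is of the score or of its change. None of the dropout inputs comes from the article; the sign depends on the score analysed and on the dropout mechanism, and equal dropout behaviour in both arms gives no bias. The correction is still needed, because it governs how the primary result is computed and described.

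**What to change.** Replace the primary ANOVA with a likelihood-based mixed model for the baseline, 3-week and 2-month scores, and take the 3-week group contrast as primary. Enter baseline as one of the repeated responses, with a mean common to both arms, so that a participant with only a baseline score stays in the model. Multiple imputation using baseline, followed by a baseline-adjusted comparison, would serve equally well. Add one missing-not-at-random sensitivity analysis, for example a range of shifts applied to the missing intervention scores.

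If ANOVA on observed scores is kept, describe the set as participants with observed outcomes, analysed as randomised, and give the number per arm. For the secondary analyses, either use the same mixed model or state how many participants the repeated measures ANOVA leaves out.

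The cost is revised wording and modest extra analysis; SPSS 22, the package named, can fit the mixed model. Baseline scores are already collected, so no new data are needed. The Trial status section reports the study as completed, so if the analysis has already been run, the new analysis should be reported openly as added afterwards.

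### The between-group ANOVA names no baseline covariate although the primary outcome is a change score with a measured baseline: valid, but less precise than baseline adjustment

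*Protocol article*

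**What the plan says.** All references are to the protocol article.

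- **Decision self-efficacy (primary outcome measure):** "The primary outcome is the change on decision self-efficacy at the end of the intervention assessed between groups". The scale runs from 0 to 100.
- **Procedure for the trial:** "Primary and secondary outcome data will be collected at baseline, at the end of the intervention and at two months from trial entry". The baseline value of the primary outcome is therefore available. One secondary scale, preparation for decision making, is an exception, because the Secondary outcome measures section gives it only after the intervention.
- **Statistical analysis:** the chi-square "test and analysis of variance (ANOVA) will be used to identify the differences between intervention groups for the categorical and continuous variables respectively". No covariate is named, and the section does not say whether the continuous variable is the change or the 3-week score. Models using several time points appear only as secondary work: "Secondary analyses will examine changes within group over time using repeated measures ANOVA and the Sidak test to correct for multiple comparisons".
- **Sample size calculation:** Cohen's d of 0.5 is assumed "for the primary endpoint only, with improved decision self-efficacy between groups at the end of the 3-week intervention". Alpha is 0.05, power 0.8, the minimum 64 per group (rounded to 70), and 84 per group after allowing for 20% attrition. The section does not say which SD standardises d, and it gives no baseline-to-follow-up correlation.

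**The concern.** For an outcome measured before and after treatment, an unadjusted comparison fixes in advance how the baseline enters. Analysing the 3-week score gives the baseline a coefficient of 0, and analysing change gives it a coefficient of 1. A linear model with the baseline as covariate estimates the coefficient from the data, and so leaves the smallest residual variance of the three.

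The plan names a test for its primary comparison that forgoes this gain, although the baseline is already being collected. At stake are the width of the confidence interval for the primary effect and the sensitivity of the estimate to chance differences at baseline.

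The sections also leave open which variable is tested. The outcome definition points to change, while the sample size text speaks of a difference at the end of the intervention. Under the unadjusted approach these give two different estimates from the same data.

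**Working it through.** **1. The plan's own figure.** Inputs from the Sample size calculation: d = 0.5, alpha 0.05, power 0.8. Sidedness is not stated, so two-sided is assumed. With a two-sample t-test, n per group has noncentrality d·√(n/2) on 2n−2 degrees of freedom.

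- n = 64: 0.5 × √32 = 2.83, power 80.1%. The stated 64 is reproduced. A one-sided test would need only 51, which does not fit.
- n = 67, from 84 × 0.8 = 67.2 completers: 0.5 × √33.5 = 2.89, power 81.9%.
- n = 70: power 83.6%.

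If d = 0.5 is on the scale that is analysed, the unadjusted comparison delivers its stated power.

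**2. Relative precision.** Let σ be the SD of the score, assumed equal at baseline and 3 weeks, and r the correlation between them. The documents give neither, so r = 0.3 to 0.7 is used as an illustrative range. Residual variances are:

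- ANOVA on change: 2σ²(1−r)
- ANOVA on the 3-week score: σ²
- Baseline-adjusted model (ANCOVA): σ²(1−r²)

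Change minus ANCOVA is σ²[2(1−r) − (1−r²)] = σ²(1−r)², and 3-week minus ANCOVA is σ²r². Neither can be negative.

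| r | ANCOVA ÷ change = (1+r)/2 | SE ratio to change | ANCOVA ÷ 3-week = 1−r² |
|---|---|---|---|
| 0.3 | 0.65 | 0.806 | 0.91 |
| 0.5 | 0.75 | 0.866 | 0.75 |
| 0.7 | 0.85 | 0.922 | 0.51 |

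Against change-score ANOVA, the standard error is thus 19%, 13% and 8% smaller.

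**3. Power if d = 0.5 is in raw-score SD units** (67 per group). Effective d is 0.5/√(2(1−r)) for change, 0.5 for the 3-week score and 0.5/√(1−r²) for ANCOVA. At r = 0.3, for example, these are 0.5/1.183 = 0.423, 0.5 and 0.5/0.954 = 0.524.

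| r | Change | 3-week | ANCOVA | n per group for 80%: change / 3-week / ANCOVA |
|---|---|---|---|---|
| 0.3 | 68.0% | 81.9% | 85.3% | 89 / 64 / 59 |
| 0.5 | 81.9% | 81.9% | 91.3% | 64 / 64 / 49 |
| 0.7 | 96.0% | 81.9% | 98.0% | 39 / 64 / 34 |

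Change-score ANOVA crosses 80% at r of about 0.47 with 67 per group (0.50 with 64, 0.45 with 70).

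**4. Power if d = 0.5 is in change-score SD units** (67 per group). Change-score ANOVA has 81.9% at every r. ANCOVA has 94.6%, 91.3% and 87.6% at r = 0.3, 0.5 and 0.7.

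**5. Change or 3-week score under adjustment.** Write B for baseline, Y for the 3-week score and G for group. If Y − B = a + τG + bB, then Y = a + τG + (1+b)B. The group effect τ is the same in both, so the adjusted model makes the choice immaterial.

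**The case against.** The strongest reply is that nothing here is wrong. An unadjusted comparison was sized and an unadjusted comparison is planned. Under 1:1 randomisation it is unbiased and has the correct type I error, and a separate analysis plan, not shown, might add a covariate. Most of this stands. The point concerns precision, and chance baseline imbalance is already reflected in the standard error. It is still more than a complaint about silence, because the Statistical analysis section chooses a test for the between-group comparison and nothing in the article points to an adjusted one.

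A reader might infer more than the documents support:

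- **That the trial falls below 80% power.** Three conditions must hold together: d in raw-score SD units, analysis of change, and r below about 0.47. The outcome definition does point to change, but the Statistical analysis section does not say that change is the variable tested, and the SD basis and r are given nowhere. If d is in change-score SD units, or the 3-week score is analysed, power is 81.9% at 67 per group.
- **That the planned test is the least efficient available.** Change-score ANOVA beats ANOVA on the 3-week score when r exceeds 0.5, and the reverse holds below 0.5. At r = 0.7 ANCOVA adds only 2 percentage points of power to change-score ANOVA (98.0% against 96.0%).
- **That the chi-square comparisons share the fault.** Several evaluation items, such as ease of use and module length, can only be asked after the intervention and have no baseline. Logistic adjustment would also change the effect measure to a conditional odds ratio.

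The variance ratios also rest on equal SDs at the two times, which the documents do not establish.

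**Conclusion.** The point holds as one of precision. The stated between-group ANOVA is valid but makes less use of the collected baseline than an adjusted model would, under either reading of the variable tested. With equal SDs and r between 0.3 and 0.7, adjustment cuts the variance by 15% to 35% relative to change scores and by 9% to 49% relative to 3-week scores. The true r is unknown, so the size of the gain is a range.

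The documents do not show a power shortfall. The figure of 68% at r = 0.3, against 85% for ANCOVA, illustrates one combination of unstated conditions and should not be read as the plan's power. Neither the validity of the primary test nor the arithmetic behind the minimum of 64 per group is in question.

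**What to change.** Make the primary analysis a linear model of the 3-week Decision Self-Efficacy score on group with the baseline score as covariate, and report the adjusted mean difference with its 95% CI. Use the same form for the secondary scales that have a baseline, such as the Health Literacy Questionnaire scales. Leave out the preparation for decision-making scale, which has none. State which SD standardises d = 0.5.

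The cost is one degree of freedom and a change of wording, with no new data or participants. Timing matters: the Trial status section reports the study completed in July 2017. If unblinded results have already been seen, keep the planned ANOVA as the primary analysis, state whether it uses change or the 3-week score, and report the adjusted model as a labelled sensitivity analysis.
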